# Determining the effects of targeted high-definition transcranial direct current stimulation on reducing post-stroke upper limb motor impairments—a randomized cross-over study

**DOI:** 10.1186/s13063-023-07886-w

**Published:** 2024-01-09

**Keywords:** Targeted high-definition tDCS, Flexion synergy, Spasticity, Stroke

## Abstract

**Background:**

Stroke is one of the leading causes of death in the USA and is a major cause of serious disability for adults. This randomized crossover study examines the effect of targeted high-definition transcranial direct current transcranial brain stimulation (tDCS) on upper extremity motor recovery in patients in the post-acute phase of stroke recovery.

**Methods:**

This randomized double-blinded cross-over study includes four intervention arms: anodal, cathodal, and bilateral brain stimulation, as well as a placebo stimulation. Participants receive each intervention in a randomized order, with a 2-week washout period between each intervention. The primary outcome measure is change in Motor Evoked Potential. Secondary outcome measures include the Fugl-Meyer Upper Extremity (FM-UE) score, a subset of FM-UE (A), related to the muscle synergies, and the Modified Ashworth Scale.

**Discussion:**

We hypothesize that anodal stimulation to the ipsilesional primary motor cortex will increase the excitability of the damaged cortico-spinal tract, reducing the UE flexion synergy and enhancing UE motor function. We further hypothesize that targeted cathodal stimulation to the contralesional premotor cortex will decrease activation of the cortico-reticulospinal tract (CRST) and the expression of the upper extremity (UE) flexion synergy and spasticity. Finally, we hypothesize bilateral stimulation will achieve both results simultaneously. Results from this study could improve understanding of the mechanism behind motor impairment and recovery in stroke and perfect the targeting of tDCS as a potential stroke intervention. With the use of appropriate screening, we anticipate no ethical or safety concerns. We plan to disseminate these research results to journals related to stroke recovery, engineering, and medicine.

**Trial registration:**

ClinicalTrials.gov NCT05479006. Registered on 26 July 2022.

## Administrative information

Note: the numbers in curly brackets in this protocol refer to SPIRIT checklist item numbers. The order of the items has been modified to group similar items (see http://www.equator-network.org/reporting-guidelines/spirit-2013-statement-defining-standard-protocol-items-for-clinical-trials/).

**Table Taba:** 

Title {1}	Determining the effects of targeted high-definition transcranial direct current stimulation (THD-tDCS) on Reducing Post-Stroke Upper Limb Motor Impairments
Trial registration {2a and 2b}.	The trial is registered with ClinicalTrials.gov. Registration number: NCT05479006
Protocol version {3}	23 July 2022, Version n. 1
Funding {4}	Research reported in this publication was supported by the American Heart Association (AHA 932980). AHA did not directly involve in the design of the study and collection, analysis, and interpretation of data or in writing the manuscript.

## Introduction

### Background and rationale {6a}

Approximately 9.4 million Americans over the age of 20 live with the impairments associated with stroke, and 795,000 people in the USA experience a new or recurrent stroke each year. This number is expected to double by the year 2050 [1]. Impairments lead to functional limitations, which make vocational pursuit, independent living, and social interaction difficult or impossible. These facts and figures make the management of stroke impairments critically important [1].

Previous intervention for stroke rehabilitation has largely focused on functional impairments [2]; however, transcranial direct current stimulation (tDCS) is an emerging and promising intervention that can transform a patient’s remaining motor control after stroke [1]. Anodal stimulation to the lesioned hemisphere can have a beneficial effect on motor function recovery [3–7]. Cathodal stimulation to the non-lesioned hemisphere can also lead to improvement in upper extremity motor function for individuals in the post-acute phase of stroke recovery. To date, the mechanism and ideal target for this stimulation remains unclear [8].

Because inhibitory tDCS targeting Wernicke’s area in the right hemisphere has led to improvement in language comprehension in people with global aphasia following left-brain lesions [8], it follows that inhibitory tDCS to the non-lesioned side could diminish interhemispheric inhibition of the lesioned side, aiding in upper extremity motor recovery [8]. Following a stroke, people often exhibit a flexion synergy in the involved upper extremity. When they attempt to elevate their involved shoulder, they experience an involuntary and simultaneous activation of their elbow, wrist, and finger flexors [9]. These involuntary movements are associated with high levels of muscle tone known as spasticity. Prior studies suggest the expression of spasticity is due to recruitment of the reticulospinal tract on the non-lesioned side of the brain, activated to compensate for corticospinal tract (CST) deficits on the lesioned side (Fig. 1b). This hypothesis is based on structural changes and functional connectivity changes occurring after stroke [9, 10]. The purpose of this study is to investigate the impact of facilitating the ipsilesional corticospinal tract via anodal stimulation and inhibiting the contralesional cortico-reticulospinal tract (CRST) via cathodal stimulation (Fig. 1).

**Fig. 1 Fig1:**
[figure not shown]
Neural mechanism and the experimental design in this study. **a** The two main motor areas involved in stroke recovery: the primary motor cortex and the dorsal premotor area. **b** Motor descending pathways in stroke recovery. **c** The first intervention involves stimulating the iM1 area using anodal stimulation. **d** The second intervention involves stimulating the cPMd using cathodal stimulation. **e** The third intervention combines anodal stimulation of the iM1 area and cathodal stimulation of the cPMd. **f** The sham condition without any stimulation intervention

## Objectives {7}

This study aims to determine how targeted high-definition transcranial direct current stimulation (THD-tDCS) changes the excitability of the contralesional cortico-reticulospinal tract (CRST) and ipsilesional cortico-spinal tract (CST), thus reducing the expression of the flexion synergy and spasticity.

Specifically, the study aims are as follows:Aim one of this study is to evaluate the degree of change of excitability of the CST following anodal Targeted High-Definition transcranial direct current stimulation (THD-tDCS) over the ipsilateral primary motor cortex (iM1) (Fig. 1c). Specifically, we aim to determine whether this stimulation simultaneously reduces contralesional CRST hyperexcitability, while enhancing motor function in the involved upper extremity in participants in the post-acute phase of stroke recovery.Aim two is to evaluate the degree of reduction in CRST hyperexcitability as evidenced by a reduction in spasticity and flexion synergy in the involved upper extremity, following cathodal THD-tDCs over the contralesional dorsal premotor cortex (cPMd) in participants in the post-acute phase of stroke recovery (Fig. 1d).Aim three combines the first two aims—to evaluate the confluent effect of bilateral THD-tDCS, when given simultaneously using anodal stimulation over iM1 and cathodal stimulation over cPMd (Fig. 1e), on the excitability of CST and CRST, as evidenced by a decrease in the expression of flexion synergy and spasticity, as well as an improvement in UE function.

## Trial design {8}

This trial, conducted at the Carle Foundation Hospital, is an exploratory sham-controlled, double-blind, cross-over study designed to evaluate the effect of THD-tDCS on upper motor function in participants in the post-acute phase of stroke recovery. The study has four intervention arms: anodal stimulation (Fig. 1c), cathodal stimulation (Fig. 1d), bilateral stimulation (both cathodal and anodal) (Fig. 1e), and sham/placebo (Fig. 1f). Participants receive each intervention in a randomized order, with a 2-week washout period between each intervention.

## Methods: participants, interventions, and outcomes

### Study setting {9}

Participants include stroke patients with upper limb motor impairment at the Carle Foundation Hospital. Data will be collected at the Carle Foundation Hospital, Urbana, IL, USA.

### Eligibility criteria {10}

Inclusion criteria are as follows: (i) stroke survivors aged between the ages of 18 and 90 years; (ii) exhibiting paresis confined to one side, experiencing substantial motor impairment of the upper extremity; and (iii) having sufficient cognition to provide informed consent. Exclusion criteria are as follows: (i) muscle abnormalities, motor, or sensory impairment in the *non*paretic upper extremity; (ii) severe atrophy or significant joint contracture; (iii) complete sensory losses in the *paretic* upper extremity or severe cognitive; (iv) affective dysfunction, severe concurrent medical problems, pacemaker, metal implant in the head, or pregnancy; (v) or a known adverse reaction to transcutaneous magnetic stimulation (TMS) or tDCS. All assessment and intervention procedures are conducted by a team of research assistants under the supervision of the principal or co-investigators.

### Who will take informed consent? {26a}

Research personnel obtain informed consent from each participant, explaining the purpose and estimated length of the study, describing the purposes and procedure behind each intervention and each assessment, and discussing each potential risk and benefit. Research personnel then explain how private health information (PHI) is used and the participant’s right to cancel the permission to use or share this information at any time, after which the participant signs a Health Insurance Portability and Accountability act (HIPA) form.

### Additional consent provisions for collection and use of participant data and biological specimens {26b}

N/A. No biological specimens will be collected.

### Interventions

#### Explanation for the choice of comparators {6b}

Participants will be compared to themselves at different visits in order to control for individual factors impacting treatment efficacy. The sham comparator is a mock tDCS session in order to ensure that patients remain blinded to their study arm. In addition, there will be a 2-week wash-out period between visits.

#### Intervention description {11a}

Electrodes are placed into a standard 10–20 EEG cap with a chin strap. Intervention dosage is 2 mA, applied for a duration of 20 min, which constitutes the optimal safe dosage required to influence neuroplasticity according to the safety guidelines of HD-tDCS [11, 12]. Research personnel estimate electrical fields in the brain using the Realistic Volumetric Approach to Simulate Transcranial Electric Stimulation (ROAST) toolbox [13].

#### Criteria for discontinuing or modifying allocated interventions {11b}

Participants have the option to think about the trial before they consent, and to withdraw at any time without any consequences to withdrawal. This study was approved by the Institutional Review Board (IRB) at Carle Foundation Hospital (IRB # 23CNI3891). Written, informed consent and HIPPA authorization are obtained from each participant.

#### Strategies to improve adherence to interventions {11c}

All intervention protocols are performed in one dedicated human subject laboratory housed within the Carle Research Institute. A member of the research team contacts participants to schedule appointments, and telephones participants the day before each appointment. If participants are late to their appointment, they are contacted to determine any need to reschedule. So far, the study has experienced no loss to follow-up, as participants are enthusiastic about the study and eager to return. As part of our effort to promote continued interest in the study, we strive to create a welcoming environment for participants and ensure that they understand they are an integral part of the findings.

#### Relevant concomitant care permitted or prohibited during the trial {11d}

Participants continue their existing health care regimens. Since the pre-intervention and post-intervention assessments are measured on the same day, the participant’s current treatment regimen does not impact on study results, although may impact carry-over between sessions.

#### Provisions for post-trial care {30}

The lead investigators’ phone numbers are provided to participants, and they are advised to contact the team if they experience any side effects. This has not yet occurred. The physician co-investigators are willing to provide care for any participant experiencing adverse effects, although any cost of care may be billed to the participant or the participant’s insurance.

### Outcomes {12}

#### Primary outcome measure

In this study, the primary outcome measure is transcranial magnetic stimulation (TMS) induced motor evoked potentials (MEP) latency and status [14, 15]. These allow the research team to determine the location of the ipsilesional corticospinal tract and the contralesional cortico-reticulospinal tract [14, 16]. Electromyography (EMG) electrodes are applied to the biceps brachii, triceps brachii, brachialis, and deltoid muscles to record muscle response to TMS. Researchers apply the paired-pulse TMS (Magstim® BiStim2, The Magstim Company Ltd., Spring Gardens, Whitland, UK) to the approximate location of the corticospinal tract origin in ipsilesional motor cortex associated with the biceps brachii and the brachialis muscles in the paretic arm. Researchers also apply the TMS to the approximate location of the origin of the cortico-reticulospinal tract utilizing a figure-eight coil [14]. Researchers utilize a paired-pulse TMS with a conditioning pulse at 65% stimulator maximum intensity and follow with a testing pulse at 85% stimulator maximum intensity. This procedure avoids any need to pre-activate the muscle which could cause bias of background EMG [16]. Researchers use paired pulse intervals of 25 ms [14]. Researchers place the center of the coil tangentially to the skull with the handle at 45° from the parasagittal plane: posterior-anterior orientation for ipsilesional M1 and anterior–posterior orientation for contralesional PMd (Fig. 1a) [17, 18]. Researchers define the M1 stimulation location as being on the grid point that results in the largest response in the target muscle. This target is found for the ipsilesional M1 and contralesional M1 hemisphere through stimulation of a 5 × 5 grid of 1 cm spaced sites on the scalp over motor areas of each hemisphere (centered at C3/4 of 10–20 EEG system) [15]. The target of the contralesional PMd is identified using a reference point of 1 cm medial and 2.5 cm anterior of the M1 target at the contralesional hemisphere [17, 19]. Previous research suggests [20] the participant is considered MEP + if MEPs of any amplitude are observed at a consistent latency on at least 5 out 10 trials. If not, the participant is considered MEP − . At least eight additional pulses with an inter-stimulus interval of 2–3 s are applied to the target to obtain an accurate estimate MEP latency. Researchers then calculate the average latency and amplitude of MEP within all positive trials.

#### Secondary outcome measure

The Fugl-Meyer upper extremity assessment (FMA-UE) is a stroke-specific performance-based impairment index with a potential score ranging from 0 to 66, with 66 representing a normal function. The assessment evaluates upper extremity motor function, sensation, passive joint motion, and joint pain and has been shown to have excellent validity and reliability [21, 22]. The FM-UE is often applied in research as an indicator of stroke severity and motor recovery and is considered the “gold standard” against which other measures are compared. The FMA-UE is performed before and after each tDCS session. A subset of the FMA-UE, portion A, is more reflective of the presence of abnormal muscle synergistic activity and is separately calculated as an outcome measure. Previous studies have validated that the minimally clinically significant difference in the FMA-UE assessment is 5 points [21, 22].

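### Flexion synergy is scored by FM-UE portion A and UE function, by inference, by the FM-UE total that contains A, so agreement between the two cannot show improvement beyond the synergy items.

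*Protocol article*

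**What the plan says.** The Secondary outcome measure part of Outcomes {12} describes the Fugl-Meyer as follows: "The assessment evaluates upper extremity motor function, sensation, passive joint motion, and joint pain". It gives a "potential score ranging from 0 to 66, with 66 representing a normal function". The component tied to synergy is introduced as "A subset of the FMA-UE, portion A" and is given its own outcome: "portion A, is more reflective of the presence of abnormal muscle synergistic activity and is separately calculated as an outcome measure".

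The abstract's Methods paragraph lists the two scores side by side: "Secondary outcome measures include the Fugl-Meyer Upper Extremity (FM-UE) score, a subset of FM-UE (A), related to the muscle synergies, and the Modified Ashworth Scale".

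Two places state synergy and function as paired effects. The abstract's Discussion expects anodal stimulation to act by "reducing the UE flexion synergy and enhancing UE motor function". Aim three in Objectives {7} looks for an effect of bilateral stimulation "as evidenced by a decrease in the expression of flexion synergy and spasticity, as well as an improvement in UE function".

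The remaining outcomes in {12} are the TMS-induced motor evoked potential (excitability) and the Modified Ashworth Scale (muscle tone). Statistical methods {20a} plans GEE for all outcomes, and {20b} adds a false discovery rate correction.

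**The concern.** The aims name two effects, but one instrument supplies both scores, and one score lies inside the other. The total is portion A plus the remaining items, so each point gained in A is a point gained in the total even if nothing else moves.

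If both scores improve, a report could present this as reduced synergy and, in addition, improved function. The data as scored cannot tell a gain limited to the synergy items from a wider motor gain. That distinction is what aim three and the anodal hypothesis need, because they name the two effects separately. No other listed outcome can supply it: the MEP measures excitability and the Modified Ashworth Scale measures tone.

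**Working it through.** **Step 1. Structure (from the protocol).** Write T for the FM-UE total, A for portion A and R for the items outside A. Because A is a subset of the FM-UE, T = A + R, and so change in T = change in A + change in R. If R does not change, the change in T equals the change in A.

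**Step 2. Which outcome carries which claim.**

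| Claim | Listed outcome |
|---|---|
| CST and CRST excitability | MEP |
| Spasticity | Modified Ashworth Scale |
| Flexion synergy | FM-UE portion A |
| UE motor function | FM-UE total (inferred; no other candidate listed) |

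**Step 3. Where synergy and function are paired.** In Objectives {7}, aim one names motor function but not synergy, and aim two names synergy and spasticity but not function. Aim three names both. The abstract's Discussion also pairs them for anodal stimulation. The point therefore reaches aim three and the abstract's anodal hypothesis.

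**Step 4. Illustration of size.** The protocol gives n = 26 and a 5% level (Sample size {14}). It gives no standard deviation or item count for A and does not say which outcome the 80% power refers to. The following are assumptions:
- a two-sided paired active-minus-sham t-test, n = 26, without FDR adjustment;
- a standardised effect of 0.572 on A, which gives 80% power on A;
- no effect on R;
- A's share s of the noise variance of T, where s = Var(A)/Var(T).

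The effect on T in units of its own SD is 0.572 × SD(A)/SD(T) = 0.572 × √s. The noncentrality is that value times √26. The probability that T is significantly better is the upper tail of the noncentral t distribution with 25 degrees of freedom beyond 2.060.

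| s | Effect on T | Noncentrality | P(T significantly better) |
|---|---|---|---|
| 0.27 | 0.297 | 1.52 | 0.31 |
| 0.40 | 0.362 | 1.85 | 0.43 |
| 0.48 | 0.396 | 2.02 | 0.49 |
| 0.545 | 0.422 | 2.15 | 0.54 |
| 0.70 | 0.479 | 2.44 | 0.65 |

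For R the probability of a significant improvement is 2.5%, the upper half of the 5% level.

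**Step 5. Effect of correlation between A and R.** Let v = Var(A)/[Var(A) + Var(R)] and let r be the noise correlation between A and R. With Var(A) + Var(R) set to 1, Var(T) = 1 + 2r√(v(1 − v)), and s = v/Var(T).
- v = 0.40, r = 0.5: Var(T) = 1.490, s = 0.27.
- v = 0.70, r = 0.5: Var(T) = 1.458, s = 0.48.

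At r = 0, v and s coincide. Positive correlation lowers A's share of the total's variance, and this is how the 31% at s = 0.27 arises.

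**Step 6. Built-in agreement.** The noise correlation of A with T is (√v + r√(1 − v))/√Var(T). Over v = 0.40 to 0.70 and r = 0 to 0.5 it runs from 0.63 (v = 0.40, r = 0) to 0.92 (v = 0.70, r = 0.5). Even when A and R are unrelated (r = 0), it is 0.63 to 0.84.

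**Step 7. Cross-check.** A separate simulation of 40,000 trials per setting used an effect of 0.57 on A, SD(A)/SD(R) from 1 to 2 and r of 0 or 0.3. The total was significant in 41-71% of trials, and the items outside A in about 5% (both directions counted).

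**The case against.** The strongest reply is that nothing is wrongly defined. The protocol openly calls A a subset, reporting a subscale beside its total is ordinary practice, and no sentence says that the two results are independent evidence. All of that stands. The point concerns how the pair can answer aims that name two effects.

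Second, the protocol never states that UE function means the FM-UE total, and it calls the Fugl-Meyer an impairment index. That link is an inference. It rests on the description of the instrument as evaluating motor function and on the absence of any other function outcome.

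Third, a reader might take the 43-65% as a false-positive rate. It is not. If A truly rises, the 0-66 total truly rises, and a significant total is a correct finding for that score. The contrast with 2.5% follows from the assumption of no effect outside A. The error would lie only in reading the total as separate evidence of function. For the same reason the FDR correction in {20b} does not resolve the point: it limits false rejections, and this rejection is not false.

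Fourth, a reader might extend the point to every aim or to the trial's main conclusion. The objectives do not support that: only aim three pairs the two effects there, and the primary outcome is the MEP. The trial is also described as exploratory, so talk of two confirmed effects would exceed the protocol's own language.

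Fifth, one could replace the total with the remainder and let the remainder alone decide whether function improved. That goes too far. The protocol cites validity, reliability and a 5-point important difference for the FM-UE, and cites nothing for total minus A.

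**Conclusion.** The point holds within limits. The synergy score is part of the only listed score that can carry the function claim, so for aim three and the abstract's anodal hypothesis, agreement between them is partly arithmetic and cannot show that function improved beyond the synergy items.

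The direction follows from the outcome definitions alone. The size rests on the assumptions in step 4: with a synergy-only effect, the total would also be significantly better in about 43-65% of trials if A carries 40-70% of the total's noise variance, and in about 31% if its share is about 27%. FDR adjustment and the planned GEE model would change these figures somewhat.

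This is a matter of interpreting secondary outcomes. It leaves the MEP primary outcome and the sample size untouched.

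**What to change.** In Outcomes {12} and Statistical methods {20a}, keep the FM-UE total and portion A as secondary outcomes. Add a third score, FM-UE total minus portion A, analysed with the same GEE model and included in the FDR correction.

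For aim three and the abstract's anodal hypothesis, state that A and the total will not be reported as two separate effects, and that improvement beyond synergy will be claimed only if the non-A score also improves versus sham.

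The new score is a subtraction of two scores already planned before and after each session, so it needs no new assessment or visit. The cost is an amendment to the outcome and analysis text while recruitment is under way, plus one more secondary test. That test uses a shorter score, which may be less sensitive to a general improvement and for which the protocol cites no validation. Keeping the total as an outcome limits that loss.
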